**Figure 3 F3:**
[figure not shown]
**Timing and content of study assessments.** ABPM, Ambulatory blood pressure monitoring; BP, Blood pressure; HBPT, Home blood pressure telemonitoring.

The study includes a first visit at the Hypertension Center (Visit 1) where automatic office blood pressure is measured, the patient’s history gathered, a physical examination performed. Laboratory tests useful for the determination of the organ damage and cardiovascular risk will be assessed as well. These tests include biochemistry and urinalysis (plasma lipids, fasting glucose, glycosylated hemoglobin, creatinine, C-reactive protein, albumin/creatinine ratio on morning urine sample or 24-h microalbuminuria), an echocardiogram with determination of left ventricular mass, a carotid ultrasonography for determination of intima-media thickness, a fundoscopy, and an electrocardiogram (ECG). Waist circumference will also be measured. A 24-h ambulatory blood pressure monitoring will be performed (see below for details).

Within 1 week from Visit 1 those patients complying with the inclusion criteria (that is, values of office systolic blood pressure ≥140 mmHg and/or office diastolic blood pressure ≥90 mmHg plus daytime systolic blood pressure ≥135 and/or daytime diastolic blood pressure ≥85 mmHg, plus presence of metabolic syndrome) will be randomized to the CM group or to the HBPT group (Visit 2).

During the same visit the patients will be administered the following psychological tests: Medical Outcome Survey Short-Form 36 (SF-36), Psychological General Well-Being Index (PGWBI), Beck Depression Inventory (BDI), Locus of Control (LoC), Self-Esteem Inventory (SEI), Illness Behaviour Questionnaire (IBQ) and Coping strategies (COPE), forming set 1, and Trait Anxiety Inventory (STAY), Type D Personality (TDP), Type A Personality (TAP), Temperament and Character Inventory (TCI), forming set 2
[24-35]. In untreated patients an antihypertensive treatment will be initiated. In treated patients, antihypertensive drug treatment will be adjusted in order to improve blood pressure control and possibly achieve office blood pressure normalization (<140/90 mmHg) on the next visit.

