Four weeks later (Visit 3) the patients will be visited again by the Investigator and the medical therapy will be adjusted on the basis of office blood pressure (target, <140/90 mmHg) in the CM group or home blood pressure (target, <135/85 mmHg) in the HBPT group. Office blood pressure will still be measured by the Investigator with the same automatic electronic instrument used for self-measurement, in all patients, including those randomized to HBPT. Additional visits are scheduled 12, 24, 36, and 48 weeks after randomization (Visits 4, 5, 6, and 7). During each of these visits office blood pressure will be measured and antihypertensive medication will be changed according to office (CM group) or home blood pressure values (HBPT group). Drug treatment can also be changed in the patients of the HBPT between the scheduled visits, based on the home blood pressure report monthly received and reviewed by the Investigator. The same laboratory tests performed at screening visit and a 24-h ambulatory blood pressure recording will be repeated at Visits 5 and 7. During these two visits psychological tests will also be administered, with the exclusion of STAY, TDP, TAP, and TCI test, administered only at Visit 2.

Occurrence of adverse events, adherence to therapy and concomitant therapies will be checked at all visits during the trial. Evaluation of adherence to drug treatment will be based on patient’s report on amount of prescribed drug intake and on counting the quantity of study medication taken by the patient, comparing this datum with the quantity expected to be returned. The Investigator will instruct each patient to bring back used and unused drug blisters at each visit. The compliance will be computed as the ratio between the number of pills taken and the number of pills which should have been taken, expressed as a percentage, and will then be graded as follows: excellent (100% of prescribed pills taken), good (80% to 99%), fair (40% to 79%), or poor (<40%).

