#### Secondary outcome measures

A series of psychological and clinical variables will be used as secondary endpoints.

Scoring of the different psychological questionnaires will be computed for the HBPT and CM groups and compared between groups. They will be used to quantify therapeutic adherence, and compared with evaluation of compliance based on the patient’s report.

The following clinical endpoints will also be evaluated: (1) the percentage of patients with office blood pressure normalization (<140/90 mmHg) after 24 and 48 weeks; (2) percentage of patients with home blood pressure normalization (average <135/85 mmHg) after 24 and 48 weeks in the HBPT group; (3) changes in average 24-h systolic and diastolic blood pressure after 24 and 48 weeks *vs*. baseline; (4) changes in office systolic and diastolic blood pressure after 24 and 48 weeks *vs*. baseline; (5) changes in average home systolic and diastolic blood pressure after 24 and 48 weeks *vs*. baseline in the HBPT group; (6) the number of antihypertensive drugs prescribed after 24 and 48 weeks *vs*. baseline; (7) the number of office or phone visits after 24 and 48 weeks *vs*. baseline; (8) direct costs of patient management, based on additional medical visits and laboratory tests performed between baseline and 24 and 48 weeks; (9) adherence to treatment, as reported by the patient (the assessment of adherence and persistence to therapy will also be done indirectly, by evaluating adherence to the home blood pressure monitoring program and by evaluation of the psychological tests); (10) difference in target organ damage score between baseline and week 24 and 48 of the study; (11) difference in cardiovascular risk level between baseline and week 24 and 48 of the study according to Heart Score (ESH-ESC) and Framingham algorithm
[40,41]; (12) difference in the rate of cardiovascular events between baseline and 24 and 48 weeks of follow-up; and (13) the number of subjects showing regression of metabolic syndrome after 24 and 48 weeks from the randomization.

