Secondarily, the trial will investigate and compare between randomization groups personality traits predictive of adherence. This will be useful to identify possible psychological determinants of adherence to antihypertensive treatment, also relating them to blood pressure response to antihypertensive treatment in daily life conditions. Poor adherence to treatment remains one of the major limitations in the management of hypertension: it may cause poor blood pressure control and may contribute to increased morbidity, mortality, and costs
[45,46].

Previous studies have shown that persistence with antihypertensive therapy decreases with time: discontinuation rates vary from 22% to 50% of patients during the first year after treatment initiation
[47-50]. Therefore, improving adherence to treatment remains a major challenge for the treating physician. Use of blood pressure telemonitoring technique, which might help in improving blood pressure control and adherence, together with quantification and definition of the psychological trait of the hypertensive patient, might help identifying features of high-risk hypertensive patients and increase the chance of successful treatment.

The study will also evaluate the impact of HBPT on additional medical and economic outcomes, which might help in unmasking possible additional advantages of this technique in high-risk hypertensive patients, on a relatively long-term follow-up.

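### Psychological scores are used both to measure adherence and to explain it, and traits recorded only at the randomisation visit are compared between arms

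*Protocol article*

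**What the plan says.** **Role of the scores as a measure.** Under Secondary outcome measures the article plans: "Scoring of the different psychological questionnaires will be computed for the HBPT and CM groups and compared between groups". The next sentence begins: "They will be used to quantify therapeutic adherence". It goes on to set the scores against compliance as the patient reports it. Endpoint 9 in the same section is adherence as the patient reports it. It adds that adherence and persistence will also be assessed indirectly, "by evaluating adherence to the home blood pressure monitoring program and by evaluation of the psychological tests".

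**Role of the scores as an explanation.** Study objectives names psychological determinants of adherence as an aim. Psychological tests says the four personality instruments are there to examine what underlies adherence behaviour. The Discussion says "the trial will investigate and compare between randomization groups personality traits predictive of adherence".

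**Timing.** Seven questionnaires are given at Visits 2, 5 and 7. The repeat administrations are described in Study procedures "with the exclusion of STAY, TDP, TAP, and TCI test, administered only at Visit 2". Visit 2 is the randomisation visit.

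**Adherence itself.** Study procedures bases it on the patient's report and on "counting the quantity of study medication taken by the patient". The result is a percentage of the pills due, in four grades. The limitations paragraph of the Discussion confirms that both methods are used.

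**Tests.** Planned statistical analyses compares secondary endpoints between the two arms by analysis of variance or Mantel-Haenszel chi-square at 0.05. Multivariate methods are optional and unspecified.

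**The concern.** A variable cannot serve as both predictor and outcome in the same question. If a depression or coping score helps to define adherence, part of any association between that score and adherence is built in.

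A separate problem is the direction of comparison. Asking what predicts adherence means relating scores to adherence across patients. Comparing scores between randomised arms answers something else: whether telemonitoring changes the scores. That is a legitimate aim for questionnaires repeated after baseline, but it has no meaning for traits recorded once, at randomisation.

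At stake is the second aim in the title, on which the article promises a comprehensive understanding. As worded, a chance imbalance in a baseline trait, or an association that exists by construction, could be reported as a finding on determinants.

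**Working it through.** The article gives no figure on this point to reproduce. The check compares its statements and adds two illustrations.

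**1. The two roles side by side.**

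| Place | Role given to the scores |
|---|---|
| Secondary outcome measures, opening | Measure of adherence |
| Secondary outcome measures, endpoint 9 | Indirect measure of adherence |
| Study objectives | Determinants of adherence |
| Psychological tests | Traits behind adherence behaviour |
| Discussion | Traits that predict adherence |

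The descriptions under Psychological tests cover quality of life, well-being, depression, locus of control, self-esteem, illness perception, coping, trait anxiety and personality. None mentions taking medication. The measuring role appears twice, so it is unlikely to be a slip of the pen.

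**2. Between-arm tests of traits recorded only at Visit 2.** Inputs: four instruments (STAY, TDP, TAP, TCI) and alpha 0.05. Among all randomised patients, and if allocation does not influence the answers, the null is true by design. With one independent test per instrument:

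P(at least one false positive) = 1 − 0.95^4 = 1 − 0.8145 = 0.1855, about 18.5%.

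Whatever the correlation between the four tests, the figure lies between 5% (fully correlated) and 4 × 0.05 = 20%. Testing subscales as well would raise it.

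**3. What each analysis can detect.** After the stated 25% drop-out, 84 × 0.75 = 63 and 168 × 0.75 = 126 remain, 189 in all. A simulation (4,000 runs per row, normal variables) drew a baseline trait with an assumed correlation rho to adherence. The article gives no rho, so a range is shown. Entries are the share of runs with P < 0.05.

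| rho | Trait between arms, n = 189 | Trait against adherence, n = 189 | Trait between arms, n = 252 | Trait against adherence, n = 252 |
|---|---|---|---|---|
| 0 | 5.2% | 5.3% | 5.1% | 5.3% |
| 0.2 | 5.8% | 78.3% | 5.1% | 89.3% |
| 0.3 | 4.8% | 98.7% | 5.0% | 99.8% |
| 0.4 | 4.7% | >99.9% | 5.1% | 100% |

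The between-arm test stays near 5% however strongly the trait predicts adherence. The direct test on the same patients has useful power.

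**4. Endpoint 9 against the procedures.** Study procedures and the limitations paragraph describe self-report plus a pill count, for every patient at every visit. Endpoint 9 names patient report and two indirect routes, and leaves the pill count out. In an open-label trial that omits the less subjective of the two measures collected.

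**The case against.** The strongest reply is that the problem sentence does not stop at quantifying adherence. It goes on to set the scores against patient-reported compliance, which links them to a separate measure. Endpoint 9 is primarily patient report, with the tests as an added, indirect route. Study procedures defines compliance without any questionnaire. Multivariate methods are allowed, and the Discussion foresees relating determinants to blood pressure response. Baseline comparisons are planned anyway to check homogeneity. Model details may sit in an analysis plan that is not shown.

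Much of this stands. The main adherence measure is not circular, and the absence of a specified regression is not the fault. What remains is what the article does state. The scores are assigned to measure adherence, so comparing them with reported compliance reads as agreement between two measures, not prediction. The between-arm comparison makes no exception for the baseline-only tests, and the Discussion speaks of comparing traits between groups as part of the determinants question, not as a homogeneity check.

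A reader might infer two further faults that the article does not support:

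- **Visit 2 tests follow open-label allocation.** The text says only "During the same visit the patients will be administered the following psychological tests". Whether the envelope is opened before or after is not stated, and the assessment schedule figure is not shown.
- **Home-monitoring adherence is missing for the 84 control patients.** It is an auxiliary measure, and the article does not single it out for a between-arm comparison. Other endpoints are openly limited to the telemonitoring arm.

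**Conclusion.** The point holds as an error in stated roles and comparisons. The scores cannot be both a measure and a determinant of adherence. Between-arm tests of the four baseline-only instruments carry no information on what predicts adherence, with about an 18.5% chance of at least one spurious difference. Endpoint 9 is out of step with the adherence measure in Study procedures.

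It would be tempting to conclude that the determinants aim cannot be answered. That goes too far: pill count and self-report exist independently of the questionnaires, and scores are already to be compared with reported compliance.

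The 18.5% assumes independent tests, one score per instrument, all randomised patients and answers unaffected by allocation. If answers were affected, or if drop-out differed by arm, a true difference could appear, but it would still not show what predicts adherence. The power figures rest on assumed correlations. The primary endpoint is not affected.

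**What to change.** 1. Delete both statements under Secondary outcome measures that psychological scores quantify or indirectly assess adherence.
2. Define endpoint 9 as in Study procedures: the pill-count percentage in both arms, with self-report alongside.
3. Analyse determinants by regressing that measure on Visit 2 psychological scores and arm. Use only baseline covariates. The number of drugs during follow-up must not be one, because treatment is changed on arm-specific readings and the number of drugs is itself a secondary endpoint.
4. Limit between-arm comparison of scores to the seven repeated questionnaires at Visits 5 and 7, adjusted for the Visit 2 score. Amend the Discussion sentence on comparing traits between groups to match.

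The cost is wording and analysis work. The data are already being collected, so the change remains feasible with recruitment started and follow-up under way. The downside is that pill count is imprecise, as the limitations paragraph admits. Error in the adherence measure would make the estimates less precise than the simulation suggests.

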### Description of the intervention: HBPT

At the time of the randomization, patients assigned to HBPT, will be equipped with an electronic blood pressure measuring device and a wireless transmitting interface. These devices will be kept at home until the end of the study.

The patient will be adequately trained by the Investigator on measurement procedures. Patients will be asked to self-measure their blood pressure at home twice a day, using a validated, automatic, electronic, oscillometric, upper arm monitor (A&D UA-767PC, A&D Company Ltd., Tokyo, Japan)
[23]. The device can store up to 126 blood pressure measurements in its memory, is operated by non-rechargeable batteries, and is equipped with a serial port for interfacing with a personal computer or a transmission unit.

Two measurements, at a 2-min interval, will be taken in the morning before going to work or before starting daily activities (between 08:00 and 10:00), and two measurements will be taken in the evening (between 18:00 and 22:00), for a minimum of 3 days a week. The measurements have to be taken in a quiet environment, with the patient in a relaxed, comfortable, sitting position for at least 5 min before self-measurement.

After each measuring session and when not used for measuring blood pressure, the blood pressure monitor will be connected through a serial cable to a GPRS wireless interface (BluMed). During the first 24 weeks, the transmitter will send blood pressure data every day to the
http://www.morepress.net website, (Biotechmed Ltd., Somma Lombardo, Varese, Italy) where they will be analyzed and a report will be generated and sent once a month via email to the Investigator. A feedback on the status of patient’s blood pressure control will also be visualized on the interface display.

The wireless interface also comes with a button which allows the patient to manually send the data to the HBPT center whenever it is deemed necessary (for example, in case of symptoms or very high blood pressure values), independently from the scheduled program. During the last 24 weeks of the follow-up no automatic data transmission will be done, but the patient will be requested to manually send to the HBPT center the self-measured blood pressure data, immediately before each scheduled office visit.

A diagram of the telemonitoring web-based system is shown in Figure 
2.

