### Description of the control condition

In the CM or control group, blood pressure will be measured only during the office visit by the same automatic device used by patients of the HBPT randomization group. After 5 min sitting, automated blood pressure measurements will be performed twice at a 2-min interval and the average of the measurements will be calculated and used as clinical reference.

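### The direct-cost endpoint leaves out telemonitoring, which only the HBPT arm incurs, and shifts the cost difference towards HBPT by that full amount; drug costs are also left out, with unknown sign

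*Protocol article*

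**What the plan says.** Under Secondary outcome measures, the protocol article lists endpoint (8) as "direct costs of patient management, based on additional medical visits and laboratory tests performed between baseline and 24 and 48 weeks". The Abstract and Study objectives also name direct costs of management but add no component. Drugs appear in endpoint (6), as "the number of antihypertensive drugs prescribed after 24 and 48 weeks", which is a count and not a cost.

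Description of the intervention: HBPT says that patients in that arm "will be equipped with an electronic blood pressure measuring device and a wireless transmitting interface", which they keep at home to the end of the study. The Investigator trains them. Readings go to a web service every day for the first 24 weeks, where they are analysed, and "a report will be generated and sent once a month via email to the Investigator". Study procedures has the Investigator review these reports. For the control arm, Description of the control condition says that "blood pressure will be measured only during the office visit by the same automatic device" that HBPT patients use.

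On the use of the results, the Discussion states: "The study will also evaluate the impact of HBPT on additional medical and economic outcomes". The discussion paragraph of the Abstract is firmer: it says that the trial will show whether HBPT improves economic as well as medical outcomes. Planned statistical analyses compares secondary endpoints between the two arms.

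**The concern.** Endpoint (8) is the only listed endpoint expressed as a cost, and the intervention being evaluated is a technology with its own equipment, service and physician time. A between-arm cost comparison that leaves out the cost of the intervention does not measure the difference in direct cost of management. The error is one-sided and does not shrink with sample size. A reader of the results would probably take a figure labelled direct costs as the overall comparison and could be misled on whether HBPT costs more or less than conventional management.

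Drug cost is a second gap. The arms are titrated on different measurements, and "Drug treatment can also be changed in the patients of the HBPT between the scheduled visits", so drug cost could differ between them.

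**Working it through.** The article states no cost figure, so there is none to reproduce. The check has three steps.

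**1. Which resources differ by design, and are they in endpoint (8)?**

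| Resource | HBPT | CM | In endpoint (8)? |
|---|---|---|---|
| Scheduled visits (weeks 4, 12, 24, 36, 48) | yes | yes | same schedule in both arms |
| Additional visits | possible | possible | yes |
| Laboratory tests | yes | yes | yes |
| Monitor for home use and wireless interface | yes | no | no |
| Transmission and web service | yes | no | no |
| Patient training | yes | no | no |
| Monthly report review | yes | no | no |
| Antihypertensive drugs | yes | yes | no (counted in endpoint 6) |

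**2. Direction of the omission.** Let V be the HBPT-minus-CM difference per patient in visit and laboratory cost, T the telemonitoring cost per HBPT patient (T > 0, and zero in CM), and D the HBPT-minus-CM difference in drug cost (either sign). Leaving other direct costs aside:

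- difference in direct cost = V + T + D
- difference that endpoint (8) reports = V
- amount omitted = T + D

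The T part always moves the result towards HBPT, by exactly T and for any value of V. The D part adds to this if D > 0 and offsets it if D < 0. The net error favours HBPT whenever D > −T.

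The documents give neither T nor D. The values below are assumed, in arbitrary units, and show only how the sign behaves. Each cell is T + D.

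| T (assumed) | D = −400 | D = −200 | D = −100 | D = 0 | D = +100 |
|---|---|---|---|---|---|
| 50 | −350 | −150 | −50 | +50 | +150 |
| 200 | −200 | 0 | +100 | +200 | +300 |
| 400 | 0 | +200 | +300 | +400 | +500 |

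**3. Quantity of uncosted resources.** The planned HBPT arm is 168 patients (Sample size), so 168 monitors and interfaces are uncosted. The number of monthly reports depends on how long automatic reporting lasts, and the article gives two durations:

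- Study design and Description of the intervention: 24 weeks. 24 / 4 = about 6 reports per patient; 6 × 168 = about 1,008.
- Home blood pressure monitoring: 12 weeks, although the same sentence places the period between Visits 2 and 5, and Visit 5 is at week 24. 12 / 4 = about 3 reports per patient; 3 × 168 = about 504.

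Both figures are before drop-out. The sample size allows 25%. If every drop-out left before the first report, 0.75 × 168 = 126 patients would remain, giving 6 × 126 = 756 or 3 × 126 = 378 reports. The manual transmissions before Visits 6 and 7 are not in these counts.

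**The case against.** The strongest defence is that the article says costs are based on visits and laboratory tests, which need not mean that everything else is priced at zero. Costing perspective and unit prices commonly belong in a full protocol or analysis plan that is not shown. This stands for prices and method. It does not stand for the components: the article chose to name them, and telemonitoring is not among them.

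A second defence is proportion. This is one of 13 clinical secondary endpoints, no cost-effectiveness ratio or economic hypothesis is specified, and visits and drug numbers are reported separately. Equipment is roughly a fixed amount per HBPT patient and could be added later. This limits the seriousness of the point and makes the repair easy, but it does not make the stated endpoint a measure of direct cost.

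Three stronger readings are tempting, and the documents do not support them:

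- *HBPT will look cost-saving by construction.* The scheduled visits are the same in both arms (Study procedures), so HBPT replaces none of them. Home blood pressure monitoring lets the Investigator schedule extra visits in response to the reports, and these count against HBPT. V could be positive, and endpoint (8) could still show HBPT as the dearer arm.
- *Leaving out drugs also favours HBPT.* Between-visit changes could raise drug cost under HBPT. However, the Discussion cites two trials of home-based against office-based adjustment that found less intensive treatment or less medication with home measurement; if that held here, the drug omission would work against HBPT. The Discussion adds that their home target equalled the office target, which is not so in this trial, so the result may not carry over. The sign is open.
- *The plan expects drug numbers to differ.* Endpoint (6) lists a count and states no expectation.

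**Conclusion.** The point holds in a limited form. As worded, endpoint (8) omits a cost that only one arm incurs, so the HBPT-minus-CM difference is too low by the full telemonitoring cost per patient, whatever happens to visits. It also omits drug cost, an error whose sign the documents do not fix; the net error therefore favours HBPT unless HBPT saves at least T per patient on drugs.

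The physical scale is 168 device sets and at most about 1,008 monthly reports (24 weeks) or about 504 (12 weeks), before drop-out. No prices are given, so no amount in money can be stated. The conclusion assumes that the named components are the whole list and that telemonitoring has a positive cost to whoever pays for care.

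The primary endpoints and the other secondary endpoints are untouched. The endpoint should nevertheless be changed, because the article announces an economic conclusion that visit and laboratory costs alone cannot support.

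**What to change.** Redefine endpoint (8) to include, besides additional visits and laboratory tests:

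- in the HBPT arm, the monitor, wireless interface, transmission, web service, training and report-review time, using a fixed tariff per device and per report with a sensitivity range;
- in both arms, the cost of antihypertensive drugs.

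Report the between-arm difference with and without the telemonitoring items, so that the reader sees the effect on care use and the overall cost separately. Reconcile the 12-week and 24-week statements on monthly reporting, because the report count depends on them.

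If the added costing is not wanted, rename the endpoint as the cost of additional visits and laboratory tests and draw no conclusion on overall direct cost.

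The price is a little more costing work. Device and report numbers follow from the design, and concomitant therapies are already checked at every visit. Unit prices would have to be obtained, since the article does not mention any source for them. HBPT may look less favourable as a result.
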